### Outcomes

➢ Primary outcome: rate of DGF defined by the need for at least one dialysis session within the first 7 days after kidney transplantation➢ Secondary outcomes:○ Rate of SGF defined by a urine output of less than 1000 mL on day 1 after transplantation, or a decreased of less than 30 and 70% in creatinine plasma concentration, respectively, on days 3 and 7 after transplantation○ Combined rate of DFG + SGF○ Mild DGF defined by a serum creatinine reduction ratio from post-transplant day 1 to day 2 less than or equal to 30% plus 24-h urine creatinine excretion on day 2 greater than 1000 mg○ Severe DGF defined by a serum reatinine reduction ratio from post-transplant day 1 to day 2 less than or equal to 30% plus 24-h urine creatinine excretion on day 2 less than or equal to 1000 mg○ Duration of in-hospital length of stay (post-transplantation hospitalization)○ Daily urine output on days 1, 3 and 7○ Creatininemia and estimated creatinine clearance by the Modification of Diet in Renal Disease (MDRD) formula [17] on days 1, 3 and 7○ Rate of primary graft dysfunctions on day 1 defined by the absence of immediate renal function (anuria)○ Time between transplantation and normalization of graft function in patients presenting a DGF○ Function of kidney transplants at 1 year: kidney graft dysfunction defined by a clearance creatinine less than 30 mL min^−1^ estimated by the MDRD formula or total dysfunction defined by a persistent hemodialysis○ In-hospital and 1-year mortality rate of transplanted patients

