#### Sample size

The sample size was determined to obtain 80% power to detect a 10% difference for rate of DGF (as defined in the primary endpoint section) at day 7 between the two groups, as this difference is considered to be clinically significant. In accordance with previous studies [7, 8], we hypothesized that 30% of the patients in the placebo group and 20% of the patients in the intervention group will develop DGF. With the threshold for statistical significance set at a *p* value of 0.05 (two-sided alpha), these calculations showed that 588 participants (recipients) are needed (294 per group). Assuming that a potential 10% of participants will be lost to follow-up (for the primary or the secondary endpoints), a total of 648 recipients needs to be included. Secondary outcomes will be compared between the two groups: using the chi^2^ test or Fisher’s exact test for categorical variables and Student’s *t* test for continuous variables.

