### Data registration

Data will be entered into the web-based electronic Case Report Form (eCRF) (RedCap, Vanderbilt University, Nashville, TN, USA) by trial or clinical personnel under the supervision of the trial site investigators at each participating center. The following data reported to influence the outcome of kidney transplantation will be registered at the different stages of the procedure:➢ In donors with a beating heart:○ Demographic data (age, sex, Body Mass Index (BMI), ethnic group, cause of death)○ Significant medical history (chronic kidney disease, hypertension, diabetes, alcohol abuse)○ Detailed SOFA score in the last 24 h before organ harvesting○ Significant biochemical abnormalities: hypernatremia > 160 mmol L^−1^, coagulation abnormalities (disseminated intravascular coagulation)○ Renal function, assessed by blood urea nitrogen levels, creatininemia and 24-h creatinine clearance in the last 24 h prior to the harvesting○ Immunological and viral status: Epstein-Barr virus (EBV) serology, number of HLA incompatibility➢ During kidney harvesting, preservation and transplantation○ Preservation data: type of preservation solution, use of a perfusion machine, cold ischemia time○ Intraoperative data: hemodynamic stability (systolic blood pressure < 80 mmHg, need for vasopressors), warm ischemia time, technical problems (duration of anastomose, surgical difficulties, hemorrhage)➢ In transplanted patients○ Demographic data (age, sex, BMI, blood group, ethnic characteristic)○ Significant medical history: hypertension, cardiac failure, diabetes, cause of the kidney disease, previous transplantation(s), duration of dialysis before transplantation, duration on the transplantation waiting list○ Viral (C hepatitis) and immunological (anti-donor antibodies) status○ Dialysis during the first week after transplantation○ Creatininemia and estimated creatinine clearance (MDRD) on days 1, 3 and 7 after transplantation○ 24-h urine output on days 1, 3 and 7 after transplantation○ Recipient and graft survival at 1 year

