### Enrollment and timeline

2015 to 2017: protocol, approvals from the ethics committee and trial tool development (eCRF, randomization system).

2017 to 2019: inclusion of patients from 16 French University Hospitals.

2019: cleaning and closure of the database.

Early 2020: data analyses, writing of the manuscript and submission for publication.

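### One-year mortality is to be compared as a simple proportion, although the plan expects losses and its timeline gives late recipients less than a year; a time-to-event comparison fits better (minor)

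*Protocol article*

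**What the plan says.** - **Outcome.** The Outcomes section lists "In-hospital and 1-year mortality rate of transplanted patients". It also lists graft function at one year, with the definition "kidney graft dysfunction defined by a clearance creatinine less than 30 mL min^−1^ estimated by the MDRD formula or total dysfunction defined by a persistent" (the criterion that closes the phrase is lasting dependence on dialysis). The abstract names renal function and mortality at one year among the secondary objectives.
- **Test.** The Sample size section states "Secondary outcomes will be compared between the two groups", by the chi-square "test or Fisher’s exact test for categorical variables and Student’s" *t* test for continuous ones. The article names no time-to-event method.
- **Expected loss.** The same section inflates the sample: "Assuming that a potential 10% of participants will be lost to follow-up (for the primary or the secondary endpoints". On that basis, "a total of 648 recipients needs to be included".
- **Analysis set.** The Data analysis section keeps everyone randomized who has a baseline evaluation. Recipients lost later therefore stay in the set without a one-year status.
- **Data collected.** The Data registration section lists "Recipient and graft survival at 1 year".
- **Timeline.** The Trial status section says that recruitment began on 19 December 2017. The Enrollment and timeline section has inclusion from 2017 to 2019, and then "2019: cleaning and closure of the database".

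**The concern.** A chi-square or Fisher test on one-year mortality needs a yes or no for each recipient. The plan itself implies that some will have none: those lost during the year, and those included in 2019, who cannot complete a year before a closure in 2019.

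The two simplest ways to fill the table err in opposite directions, even when loss has nothing to do with prognosis. A recipient who dies early is a known death, whereas one who leaves alive drops out of a complete-case denominator, so that proportion is too high. Counting leavers as alive misses their later deaths, so that proportion is too low. If loss differs by arm, the error enters the comparison.

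The one-year outcomes are the trial's only evidence beyond the early post-transplant and hospital period. A time-to-event estimate would use the partial follow-up instead of forcing a status.

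**Working it through.** **The plan's own figures.** For 30% against 20%, two-sided alpha 0.05 and 80% power:

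n per arm = [1.960 × √(2 × 0.25 × 0.75) + 0.842 × √(0.3 × 0.7 + 0.2 × 0.8)]² / 0.10² = (1.200 + 0.512)² / 0.01 ≈ 293.2, so 294 per arm and 588 in total, as stated.

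For the allowance, 588 × 1.1 = 646.8, which matches 648 after rounding to an even total (588 / 0.9 would give 654). Ten percent of 648 is about 65 recipients, which leaves about 583.

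**Assumptions.** The article gives no one-year mortality, so I take true values m of 2%, 5% and 10%. I assign the whole 10% allowance to the one-year outcome and let death and loss act independently at constant rates over the year.

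**Formulas.** Let h = −ln(1 − m) and c = −ln(1 − L), with L the loss probability.
- Observed deaths: d = h/(h + c) × (1 − e^−(h+c)). This is also the result if the lost count as alive.
- Known alive at one year: a = (1 − m)(1 − L).
- Complete-case result: d / (d + a).
- With independent loss, Kaplan-Meier targets m.

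**Example, m = 5%, L = 10%.** h = 0.0513, c = 0.1054, a = 0.95 × 0.90 = 0.855. Then d = 0.3274 × 0.145 = 0.0475, and complete case = 0.0475 / 0.9025 = 0.0526.

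| True mortality | Lost counted as alive | Complete case |
|---|---|---|
| 2% | 1.90% | 2.11% |
| 5% | 4.75% | 5.26% |
| 10% | 9.50% | 10.50% |

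For scale, the standard error of a 5% proportion in 324 recipients, taken as independent, is √(0.05 × 0.95 / 324) = 1.2 points.

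**Between arms.** Equal loss shifts both arms alike. With assumed losses of 5% and 15% and equal true mortality of 5%:
- Complete case: 5.12% against 5.41%, a false difference of about 0.3 points.
- Lost counted as alive: 4.88% against 4.62%, again about 0.3 points.

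At 10% true mortality the false difference is about 0.5 points either way.

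**Precision.** For an assumed 10% against 5%, chi-square power is about 63% on 292 completers per arm and about 68% on all 324 with nobody lost. A log-rank approximation with about 46 events gives 69%. That exceeds the no-loss chi-square figure, so part of the gap comes from the formulas. A fair reading is a gain of at most about 5 points.

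**Timeline.** Even if the database closes on the last day of 2019, nobody included after 31 December 2018 has a full year. How many that is depends on when inclusion ends, which the article does not say. Assume even accrual from 19 December 2017, closure on 31 December 2019, 5% mortality and 10% loss as above:

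| Assumed end of inclusion | Share short of one year | Counted as alive | Complete case |
|---|---|---|---|
| 31 March 2019 | 90/467 = 19% | 4.6% | 6.3% |
| 30 June 2019 | 181/558 = 32% | 4.4% | 7.1% |
| 30 September 2019 | 273/650 = 42% | 4.0% | 7.5% |

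Middle row: late recipients have between 0.50 and 1 year of possible follow-up. Averaging h/(h + c) × (1 − e^−(h+c)u) over that range of u gives 3.63% observed deaths, so d = 0.676 × 4.75% + 0.324 × 3.63% = 4.39%. Known alive at one year is 0.676 × 85.5% = 57.8%. Complete case = 4.39 / (4.39 + 57.8) = 7.1%.

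**The case against.** The strongest reply is that mortality at a fixed horizon is a legitimate quantity, that a chi-square can be combined with imputation or tracing of vital status, and that rules for missing data usually sit in an analysis plan, which is not shown. This stands in part. A reader might infer that the plan discards lost recipients or counts them as event-free. The article says neither, and its silence on missing status is no finding. What remains is the test it does name, which does not fit the follow-up it describes.

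A reader might also extend the point to graft function at one year. The article does not support that. The outcome is a status at a fixed time, clearance below a threshold or persistent dialysis, so comparing proportions suits it. Censoring cannot supply a one-year clearance for someone last seen at month 8; the difficulty there is missing status and death before one year. Only graft survival, which Data registration records but Outcomes does not list, would take a time-to-event method.

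Three further limits stand:
- The 10% is a planning allowance across the primary and secondary endpoints, not a forecast for one-year mortality.
- Recipients and their clinicians are blinded, and nothing in the article points to unequal loss. If loss were informative, Kaplan-Meier would be biased too.
- The figures for late recipients rest on assumed dates and belong mainly to the timeline conflict, whose proper remedy is to reconcile the dates.

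Nor does the summary list in Data registration show that dates of death or graft failure go unrecorded.

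**Conclusion.** The point holds for one-year mortality and, if reported, graft survival. The article assigns a comparison of proportions to an outcome for which its own loss allowance and timeline leave some recipients without a status.

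With 10% independent loss, the proportion in an arm is off by about 5% in relative terms: 0.1 to 0.5 points for assumed true mortality of 2% to 10%, and about 0.25 points at 5%, well inside a standard error of 1.2 points. Bias in the between-arm comparison is small unless loss differs by arm. The larger errors in the timeline table arise only if late recipients are in fact cut off by closure, and they depend on the assumed dates.

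This is a cheap improvement of minor severity. It does not touch the primary endpoint, which is settled within seven days, or the sample size.

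**What to change.** - **Mortality at one year:** estimate by Kaplan-Meier and compare by log-rank test or Cox model, censoring at last contact.
- **Graft survival, if reported:** use cumulative incidence of graft failure with death as a competing event, and a matching comparison.
- **Dates:** make sure that dates of death, graft failure and last contact are available for these analyses.
- **Unchanged:** keep the comparison of proportions for in-hospital mortality and for graft function at one year.
- **Timeline:** reconcile the 2019 database closure with the one-year outcomes. A survival method cannot replace this step, because one-year graft function would stay unobserved for recipients cut off early.

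The cost is a few sentences of analysis wording, up to three date fields if they are not already collected, and slightly more analysis work.

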### Pharmaceutical aspects

The clinical trial pharmacist of the promoting hospital will package all study drugs in trial packs. Standard operating procedures (SOPs) have been developed for every stage of a controlled drug’s journey from procurement (ordering, receipt and transport) to safe storage, supply, administration, destruction and for dealing with an incident. The SOPs will be accessible to the staff at all times.

### Statistical analysis

The methodological support will be provided by the Clinical Research Unit of Marseille University Hospital (Unité Aide Méthodologique à la Recherche Clinique, AP-HM, France).

#### Sample size

The sample size was determined to obtain 80% power to detect a 10% difference for rate of DGF (as defined in the primary endpoint section) at day 7 between the two groups, as this difference is considered to be clinically significant. In accordance with previous studies [7, 8], we hypothesized that 30% of the patients in the placebo group and 20% of the patients in the intervention group will develop DGF. With the threshold for statistical significance set at a *p* value of 0.05 (two-sided alpha), these calculations showed that 588 participants (recipients) are needed (294 per group). Assuming that a potential 10% of participants will be lost to follow-up (for the primary or the secondary endpoints), a total of 648 recipients needs to be included. Secondary outcomes will be compared between the two groups: using the chi^2^ test or Fisher’s exact test for categorical variables and Student’s *t* test for continuous variables.

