**Methods:**

The Cis-A-rein study is an investigator-initiated, prospective, multicenter, double-blind, randomized, controlled study performed to assess the effects of a donor preconditioning with cyclosporine A on kidney grafts function in transplanted patients. After randomization, a brain dead donor will receive 2.5 mg kg^−1^ of cyclosporine A or the same volume of 5% glucose solution. The primary objective is to compare the rate of DGF, defined as the need for at least one dialysis session within the 7 days following transplantation, between both groups. The secondary objectives include rate of slow graft function, mild and severe DGF, urine output and serum creatinine during the first week after transplantation, rate of primary graft dysfunction, renal function and mortality at 1 year. The sample size (*n* = 648) was determined to obtain 80% power to detect a 10% difference for rate of DGF at day 7 between the two groups (30% of the patients in the placebo group and 20% of the patients in the intervention group).

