### Randomization and blinding

Computer-generated randomized lists will be drawn up before the onset of the study using a permuted block design, under the responsibility of the Clinical Research Unit (Unité Aide Méthodologique à la Recherche Clinique, AP-HM, France). Randomization (1:1 allocation ratio) will be stratified by center (*n* = 16) and the number of kidneys per donor (two modalities, one or two). Randomization is centralized, web-based and accessible 24 h a day according to the allocation list. A randomization number will be allocated to each patient. The intensivist and the nurse in charge of the donor with a beating heart will be blinded regarding the allocation of treatment (preparation by an intensive care unit (ICU) nurse or a clinician not in charge of the donor). The statistician, the transplanted patients and the clinicians in charge of the transplanted patient will all be blinded concerning the treatment allocation.

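### The 588 recipients carry no allowance for two recipients sharing a randomized donor, so the stated 80% power is not supported under a donor-clustered test unless the within-donor correlation is about zero

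*Protocol article*

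**What the plan says.** The Sample size section of the protocol article sets a "threshold for statistical significance set at a *p* value of 0.05 (two-sided alpha") and assumes that "30% of the patients in the placebo group and 20% of the patients in the intervention group will develop DGF". From this it concludes that "these calculations showed that 588 participants (recipients) are needed (294 per group"). The total is then raised to 648, and the only reason given is dropout: "Assuming that a potential 10% of participants will be lost to follow-up", for the primary or the secondary endpoints. The Abstract (Methods) repeats that the sample size "was determined to obtain 80% power to detect a 10% difference for rate of DGF at day 7 between the two groups".

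Under Trial intervention, it is the donor who receives the single dose after randomization. Under Trial design, the result is read in the recipients of that donor's kidneys. Under Randomization and blinding, the strata are center and "the number of kidneys per donor (two modalities, one or two"). Under Data analysis, the primary comparison is a chi-square or Fisher's exact test of the two proportions of recipients. No donor term is named for it.

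**The concern.** Two recipients of kidneys from one donor always fall in the same arm, because the arm is fixed by the donor's treatment. They also share whatever in that donor affects early graft function. The protocol itself expects such factors to matter: its secondary logistic model lists donor age, norepinephrine use, diabetes and high blood pressure as possibly linked to delayed graft function. Some positive correlation within donors is therefore plausible on the protocol's own premises. With positive correlation, 588 recipients carry less information than 588 independent patients.

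Two things are at stake. The power quoted in the Abstract and in the Sample size section may be higher than a valid test can deliver. And if the comparison ignores donors, as the Data analysis section now has it, its nominal 5% level is not its true level.

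This is not a matter of detail that a fuller protocol or an analysis plan could supply. The stated figure itself can be traced to a formula for a different design.

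**Working it through.** **Inputs from the protocol article.** Rates 0.30 and 0.20, two-sided alpha 0.05, power 80%, 588 evaluable recipients and 648 included (Sample size); 1:1 allocation and one or two kidneys per donor (Randomization and blinding).

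**Inputs that are not in the document.** These are assumed and varied: the within-donor ICC, and f, the share of recipients whose co-recipient from the same donor is also in the trial.

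**Step 1: reproduce the stated figure.** For independent recipients with pooled variance under the null, the mean rate is 0.25 and

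n per group = [1.960 × √(2 × 0.25 × 0.75) + 0.842 × √(0.21 + 0.16)]² / 0.10² = 293.2, rounded up to 294.

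Two groups give 588, with power 80.1%. The match is exact, so nothing in 588 allows for clustering. For the included number, 294 × 1.1 = 323.4, rounded up to 324 per group, gives 648. That step is used up by dropout: 648 × 0.9 = 583.

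**Step 2: design effect.** With clusters of one or two, the variance of an arm's proportion is multiplied by DE = 1 + f × ICC.

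**Step 3: power of a test that respects donors.**

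Power = Φ{[0.10 − 1.960 × √(0.375 × DE / n)] / √(0.37 × DE / n)}, with n per group.

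Example with n = 294, f = 1, ICC = 0.1, so DE = 1.1: the standard errors are 0.0375 (null) and 0.0372 (alternative), and Φ[(0.10 − 0.0734) / 0.0372] = 76.3%.

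| ICC | 588, f = 1 | 588, f = 0.5 | 648, f = 1 | 648, f = 0.5 |
|---|---|---|---|---|
| 0.05 | 78.2% | 79.1% | 82.0% | 82.9% |
| 0.1 | 76.3% | 78.2% | 80.2% | 82.0% |
| 0.2 | 72.6% | 76.3% | 76.7% | 80.2% |
| 0.3 | 69.1% | 74.4% | 73.3% | 78.4% |
| 0.5 | 62.9% | 70.8% | 67.1% | 75.0% |

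The 648 columns suppose that every included recipient is evaluable. There, 80% holds up to DE = 324 / 294 = 1.10. At 588 with f = 1, the difference detectable with 80% power is 10.4, 10.9, 11.3 and 12.0 points at ICC 0.1, 0.2, 0.3 and 0.5.

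**Step 4: the planned test, which ignores donors.** Its true two-sided level is 2 × [1 − Φ(1.960 / √DE)]. Its power uses the null standard error without DE and the true standard error with DE. At 588 and f = 1:

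| ICC | True level | Power |
|---|---|---|
| 0.05 | 5.6% | 79.5% |
| 0.1 | 6.2% | 79.0% |
| 0.2 | 7.4% | 78.0% |
| 0.3 | 8.6% | 77.1% |
| 0.5 | 11.0% | 75.5% |

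A simulation of paired binary outcomes (100,000 runs per scenario, 25% rate in both arms) gave levels of 5.6%, 6.0%, 7.4%, 8.5% and 11.0%. At f = 0.5 the formula gives 5.6%, 6.2%, 6.8% and 8.0% at ICC 0.1, 0.2, 0.3 and 0.5.

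**The case against.** The best defence has four parts.

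- **The arithmetic is correct.** For its stated inputs and for the test named under Data analysis, 294 per group is right. This stands. The fault lies in an independence assumption that the design does not meet, not in the sum.
- **The size of the loss is unknown.** A reader might infer that power has fallen to somewhere between 63% and 76%. The document does not support that. It gives no ICC, and those figures need every recipient to be paired. The stratification foresees one-kidney donors. The recipient criteria (age 18 to 70, consent, no double-kidney or multiorgan indication) mean that even a two-kidney donor may contribute only one trial recipient. At ICC 0.05 the loss is about 2 points or less.
- **The margin may help.** The 10% covers loss for secondary endpoints too, and these run to 1 year, while the primary endpoint is known by day 7. More than 588 may therefore be evaluable for it. This stands in part: the split is not given, and at 648 the cover ends at a design effect of about 1.1.
- **Under the planned test, power hardly falls.** This is true, but the power is kept at the price of a true level above 5%. It moves the problem rather than removing it, and makes a false positive the main risk of the analysis as written.

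A reader might also infer that the trial must recruit more patients, or that a null result could not exclude a 10-point benefit. Neither follows. The first depends on an ICC and a pairing share that nobody has stated. The second is judged from the confidence interval, provided that the interval allows for donors.

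**Conclusion.** The point holds in a conditional form. The 588 contains no design effect, the randomized unit is the donor, and the only inflation is assigned to dropout. At 588 evaluable recipients, 80% power for 30% versus 20% is therefore not supported under a valid donor-clustered test unless the ICC is about zero or hardly any recipients are paired. Over the assumed range (ICC 0.05 to 0.5), the shortfall from 80% runs from about 1 point (ICC 0.05, half paired) to about 17 points (ICC 0.5, all paired). It could vanish at low design effects if nearly all 648 are evaluable at day 7. Under the comparison as planned, the same omission shows mainly as type I error of about 6%, 7%, 9% and 11% at ICC 0.1, 0.2, 0.3 and 0.5 with all paired. That the stated power has no basis in this design is certain; how far it is off is not.

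**What to change.** Keep 648 recipients and make three changes.

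1. In the Abstract and the Sample size section, replace the flat 80% with the power, or the detectable difference, under DE = 1 + f × ICC. Show it over a stated range of ICC that includes 0.05, and of f. State how many recipients are expected to be evaluable at day 7.
2. Give the expected number of donors as well as recipients. For 648 recipients this is 648 / 2 = 324 donors if all are paired, and 162 + 324 = 486 if half are.
3. Under Data analysis, make the primary comparison account for donor clustering, for example by GEE with donor as the cluster or by a cluster-adjusted chi-square. Tie the restated power to that analysis. Without this step the new figure would describe a test that the trial does not plan to run.

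The cost is a somewhat lower stated power and a slightly less simple primary test. No extra patients are needed, and nothing in treatment or follow-up changes. The analysis does need a donor identifier on each recipient's record.

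### Unadjusted t tests for the continuous secondary outcomes leave a modest gain in precision unused, although pre-transplant donor and recipient predictors are already recorded

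*Protocol article*

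**What the plan says.** The last sentence of the Sample size section fixes the method: "Secondary outcomes will be compared between the two groups", by chi² or Fisher's exact test for categorical outcomes and by "Student’s *t* test for continuous variables". No covariate or stratification factor is mentioned.

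The Outcomes section lists the continuous measures concerned: "Daily urine output on days 1, 3 and 7"; "Creatininemia and estimated creatinine clearance by the Modification of Diet in Renal Disease (MDRD) formula" on the same three days; and length of the post-transplant hospital stay. Time to normalization of graft function is also listed, but only for recipients with DGF, and is left aside here.

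The Data registration section introduces its variables with "The following data reported to influence the outcome of kidney transplantation will be registered at the different stages of the procedure". For donors these include age, hypertension, diabetes and "Renal function, assessed by blood urea nitrogen levels, creatininemia and 24-h creatinine clearance in the last 24 h prior to the harvesting". For recipients they include age, sex, BMI and "duration of dialysis before transplantation, duration on the transplantation waiting list".

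Under Data analysis, the only model with covariates is a logistic regression, labelled secondary, that looks for variables linked to DGF. A normality check is planned, but no alternative to the t test is named. Under Randomization and blinding, allocation is stratified by center (16) and by whether the donor gives one or two kidneys. No stated analysis uses these factors.

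**The concern.** An unadjusted t test leaves all between-recipient variation in its error term, including the part that could have been predicted before transplantation. Recipient body size and sex affect creatinine whatever the graft does, and donor age and donor renal function plausibly affect early graft function. The trial will hold these variables anyway.

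At stake is the width of the confidence intervals for the early-function outcomes and length of stay. Because the article names the test, this is a choice it makes and not a detail left open. Fixing the covariates before unblinding would also remove the temptation to choose an adjustment after seeing the results.

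**Working it through.** **Reproducing the plan's own figure.** Inputs from the Sample size section: DGF 30% against 20%, two-sided alpha 0.05, power 80%. With pooled variance and no continuity correction:

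n per group = [1.960·√(2·0.25·0.75) + 0.842·√(0.30·0.70 + 0.20·0.80)]² / 0.10² ≈ 293.2, rounded up to 294, so 588 in total.

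This agrees with the article; power at 294 per group is 80.1%. Adding 10% gives 294 × 1.10 = 323.4, so 324 per group and 648 in total, also as stated. These figures belong to the primary endpoint. They are used here only to supply 294 evaluable recipients per group.

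**What an unadjusted t test can detect.** In units of the outcome SD, with 80% power:

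(1.960 + 0.842)·√(2/294) = 0.231 SD.

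**Effect of adjustment.** Let R² be the share of outcome variance explained by the covariates. The article gives no R², SD or correlation, so R² is an assumption.

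- Standard error multiplier = √(1 − R²)
- Power at 0.231 SD = Φ(2.802/√(1 − R²) − 1.960)
- Unadjusted sample size with the same precision = 588/(1 − R²)

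| Assumed R² | SE multiplier | Detectable difference (80% power) | Power at 0.231 SD | Equivalent unadjusted n |
|---|---|---|---|---|
| 0 | 1.000 | 0.231 SD | 80% | 588 |
| 0.05 | 0.975 | 0.225 SD | 82% | 619 |
| 0.10 | 0.949 | 0.219 SD | 84% | 653 |
| 0.20 | 0.894 | 0.207 SD | 88% | 735 |

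The standard error thus falls by about 2.5%, 5% and 11%. If the covariates explain nothing, a short list costs practically nothing at this sample size.

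**Shared donors.** The table treats recipients as independent, but donors are randomized and one donor can supply two recipients. If all recipients came in pairs, the variance of the treatment comparison would be multiplied by 1 + ICC. For an assumed ICC of 0.1 to 0.2 the standard error is inflated by √1.1 = 1.049 to √1.2 = 1.095, that is 5% to 10%. This is as large as the gain from an R² of 0.10 to 0.20. An adjusted model that ignored the shared donor could therefore report intervals that are too narrow.

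**Chance imbalance in a donor variable.** With at most two recipients per donor, 648 recipients come from at least 648/2 = 324 donors. The standard error of the between-arm difference in mean donor age is then at most about √(4/324) = 0.11 SD, against √(4/648) = 0.08 SD for 648 independent units. If donor age explained 5% to 10% of outcome variance (assumed), the typical shift in the outcome difference would be 0.11 × √0.05 ≈ 0.025 SD to 0.11 × √0.10 ≈ 0.035 SD. That is small beside 0.231 SD.

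**The case against.** The strongest reply is that, as regards covariates, comparing randomized groups without adjustment is valid, and that adjusted analyses of secondary outcomes are often added in an analysis plan. The first part stands: the issue is efficiency and not error. The second carries less weight, because the article names the unadjusted test for these outcomes.

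Further objections limit the size of the point, and they stand:

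- **The gain is not documented.** No R² can be taken from the article, and one range need not fit all four outcomes. The recipient's own pre-transplant creatinine and urine output are not listed, so the usual main source of gain, a baseline value of the outcome, is missing. The article also expects 20% to 30% of recipients to be dialysed in week 1, and dialysis lowers creatinine whatever the covariates say. An R² near 0.05 is quite possible.
- **The Data registration heading proves little.** A reader might infer that the article declares each listed variable a predictor of these outcomes. The same heading covers the outcomes themselves, such as week-1 dialysis and creatinine on days 1, 3 and 7. That the donor and recipient variables are predictive is likely but not shown.
- **These are not the only graded measures.** A reader might infer that early graft function is graded nowhere else. The Outcomes section also separates mild from severe DGF and includes time to normalization. Length of stay is not a measure of graft function.
- **Adjustment is not wholly free.** Missing covariate values must be handled, and a linear model for mean length of stay would not deal with its likely skew.

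**Conclusion.** The point holds as a modest, inexpensive gain in precision for secondary outcomes. The direction is clear. The size rests on assumed R² values of 0.05 to 0.20, which give a standard error smaller by about 2.5% to 11% and power of about 82% to 88% where the t test has 80%. These figures treat recipients as independent, and the lower end is the safer expectation.

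Two stronger readings are not supported. One is that the unadjusted tests are biased or invalid for lack of covariates; randomization protects them, and chance imbalance of the size calculated is covered by the test's error rate. The other is that the trial's main result is at risk; the primary DGF comparison and the sample size do not depend on this choice.

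**What to change.** For urine output, creatinine and MDRD clearance, replace the t tests by linear models that contain:

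- treatment;
- the stratification factors, center and number of kidneys per donor;
- a short list fixed before unblinding: donor age, donor renal function before the infusion, donor hypertension and diabetes, and recipient age, sex, BMI and dialysis duration.

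Use a donor random effect or cluster-robust standard errors, so that two recipients of one donor are not counted as independent. Leave out ischemia times and anything else that arises after the infusion. Donor renal function is recorded over the 24 h before harvesting and the infusion falls within the last 2 h, so the wording should specify the pre-infusion value. State a simple rule for missing covariates, such as imputation.

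Report the adjusted difference with its 95% CI as the main result for each of these outcomes, and the unadjusted difference as a sensitivity result. Analyse length of stay on a log scale or by another method suited to skewed data.

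The cost is a short change of wording, slightly more analysis work and the handling of missing covariates. The covariates and stratification factors are already collected, and no patients or procedures are added.
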